## Abstract

Multiple sclerosis (MS) is characterized by a progressive worsening of disability over time. As many regulatory-cleared disease-modifying treatments aiming to slow down this progression are now available, a clear need has arisen for a personalized and data-driven approach to treatment optimization in order to more efficiently slow down disease progression and eventually, progressive disability worsening. This strongly depends on the availability of biomarkers that can detect and differentiate between the different forms of disease worsening, and on predictive models to estimate the disease trajectory for each patient under certain treatment conditions. To this end, we here describe a multicenter, retrospective, observational study, aimed at setting up a harmonized database to allow the development, training, optimization, and validation of such novel biomarkers and AI-based decision models. Additionally, the data will be used to develop the tools required to better monitor this progression and to generate further insights on disease worsening and progression, patient prognosis, treatment decisions and responses, and patient profiles of patients with MS.

## Introduction

### Background

Multiple sclerosis (MS) is a devastating immune-mediated disorder of the central nervous system (CNS) resulting in neurological disability and a wide range of physical and cognitive impairments (1). Irreversible worsening of clinical disability can occur at any stage of the disease and is driven mainly by two processes. First, patients with MS (pwMS) may accumulate disability due to acute inflammatory relapses, known as Relapse Associated Worsening (RAW), and second, pwMS may accumulate disability not associated with relapses which is referred to as Progression Independent of Relapse Activity (PIRA) (2).

While there are currently about 20 regulatory-approved Disease-Modifying Treatments (DMTs) available, most of them were developed to target acute inflammatory relapses, thus lesion formation. Therefore, and not surprisingly, clinical decision-making and treatment optimization are highly focused on these acute inflammatory lesions. Additionally, all existing guidelines on the use of DMTs in MS are based on expert judgment and differ across countries (3, 4). As of 2017, the first DMT for the treatment of progressive MS was regulatory approved in the US and Europe (5), and nowadays more clinical trials aiming to treat progressive MS are on their way. The latter is driven by accumulating evidence that PIRA can drive disability accumulation already at early disease stages (6) and even in the absence of RAW (7). Even though PIRA entered the spotlights only recently and is therefore not fully understood yet, brain and spinal cord atrophy, as well as chronic active lesions (i.e., paramagnetic rim lesions), have been shown to substantially contribute to PIRA (8, 9).

The heterogeneity of MS combined with the availability of multiple DMTs (with limited scope) indicate the need for a data-driven and personalized approach to treatment optimization, to more efficiently slow down disease progression and disability worsening. While early diagnosis and patient-level prognostic modeling are important to provide data-driven personalized recommendations on treatment optimization, the ability to disentangle and monitor the disability accumulation due to RAW or PIRA will be key to achieving the best possible long-term outcomes (10, 11). The latter strongly depends on the availability of biomarkers, including imaging markers of different entities, that can detect and differentiate between different forms of disability worsening and underlying disease aspects, enabling the early detection of PIRA throughout the disease course.

### Study objectives

The study described in this paper is being conducted within the scope of the EU-funded research project “Clinical impact through AI-assisted MS Care” (CLAIMS^1^). CLAIMS aims to address the urgent need for more data-driven and personalized care for pwMS. To this end, CLAIMS will develop, validate, and seek regulatory approval for a companion platform that provides a holistic view of each patient by visualizing both existing and new biomarker data, as well as predict disease trajectories under different treatment scenarios.

The objective of the RECLAIM study is to collect and harmonize a substantial retrospective dataset on pwMS for research purposes. This dataset will be used for the development, training, optimisation and validation of novel biomarkers and AI-based decision models that support prognosis of individual pwMS’ disease course and treatment responses in a real-world setting. Additionally, the data will be used to develop new tools to better monitor this progression and to generate further insights on disease worsening and progression, patient prognosis, treatment decisions and responses, and patient profiles of pwMS.

## Methods and analysis

### Study design

RECLAIM is a multicenter, retrospective, observational study, aimed at setting up a harmonized database to allow the secondary use of data for research and development purposes. This database will include real-world healthcare data from routine clinical practice, structured data from observational studies as well as control arm data from clinical trials.

### Participants

We expect the inclusion of the majority of records of ±7,000 patients from real-world routine clinical care and observational studies (6 clinical centers in 4 countries). This will be supplemented with data from randomized controlled trials from ±4,000 patients (coming from 4 pharmaceutical companies). In addition to the focus on data from pwMS, the foreseen retrospective dataset will also include real-world clinical data from patients with Clinically Isolated Syndrome (CIS) and Radiologically Isolated Syndrome (RIS) as well as Neuromyelitis Optica Spectrum Disorder (NMOSD) and Myelin oligodendrocyte glycoprotein antibody-associated disease (MOGAD). The inclusion of CIS and RIS patients allows us to gain insights into and develop models that consider the very early stages of MS. Despite the recommendations on standardized brain and spinal cord imaging in MS diagnosis and monitoring (12), misdiagnosis of MS in the presence of mimicking CNS pathologies can occur. Given that both NMOSD and MOGAD have overlapping disease patterns and MRI presentations when compared with MS, the inclusion of data from NMOSD and MOGAD patients is relevant. By incorporating this data, we will be able to build more robust prognostic models for MS specifically, as we can identify the differences in clinical and radiographic presentation and disability worsening that set NMOSD and MOGAD apart from MS.

### Inclusion/exclusion criteria

Inclusion criteria that will be applied:

Participants must have a confirmed diagnosis of MS, NMOSD, MOGAD, CIS or RIS.Participant (or participant’s legal representative) has previously signed and dated an informed consent form (ICF) for the secondary use of their data, or assent form. Alternatively, the secondary use of the patient’s data is allowed following Institutional Review Board (IRB)/Ethical Committee (EC) approval in accordance with national and local subject privacy regulations.

Participants will be excluded according to the following exclusion criteria:

Participants under 18 years of age will be excluded.Other unspecified reasons that, in the opinion of the Investigator or Joint Steering Committee, make the participant unsuitable for study participation.

### Endpoints

The accomplishment of a sufficiently large, harmonized database for research purposes will be determined by:

The number of patients from each institution who have contributed data to the database.The number of patients from each institution whose data was mapped to the common data model of the harmonized database.The number of patients from the control arms of clinical trials who have contributed data to the database.The data completeness of each variable in the harmonized database.

The accomplishment of a sufficiently high quality, harmonized database for research purposes will be determined by:

The representativeness of the harmonized dataset for the MS patient population as evaluated by age range, gender balance, the distribution of country of residence, the distribution of race/ethnicity and the distribution of educational level.The validity of the data through an assessment of the amount of erroneous or impossible data entries for each variable.The temporal uniformity of each institution’s data over time as assessed by the number of changes to variables over time (addition of new variables or variables no longer being captured, alterations to how variables are captured).The temporal uniformity of the harmonized dataset over time as assessed by the average time between subsequent assessments of each variable.The presence of contextual information on standard data gathering and analysis processes of each institution.The presence of a unique and pseudonymized patient ID for all data of each patient, allowing to link such data of each patient.

The feasibility of using the harmonized database for the development of the anticipated novel biomarkers and AI-based decision models, will be determined by:

The temporal uniformity of MRI data over time as assessed by the comparability of MRI scans and the average time between subsequent MRI assessments for each patient.The percentage of MRI data sets that are compliant with the MAGNIMS-CMSC-NAIMS acquisition guidelines.The percentage of MRI data sets for which the automated quality control process of icobrain ms did not indicate any quality issues upon analysis.The percentage of patients with a complete disease-modifying treatment history available, from the date of diagnosis to the current day.The percentage of patients with a complete disease history available, from the date of diagnosis to the current day.The validity and temporal uniformity for disability assessment as clinically determined by EDSS, Functional systems score, T25FWT, 9HPT and SDMT. Each of these scores will be assessed individually for the amount of erroneous or impossible data entries, as well as for the average time between subsequent assessments of each variable.

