## Discussion

Real-world clinical data has the advantage that it often allows to study larger groups of patients over long timeframes (versus clinical trial data), but one of the major difficulties in using real-world clinical data is that it is known to often be incomplete (e.g., variables are not captured each visit), to contain errors, to contain duplicates, etc. In addition, this data is captured during routine clinical care, therefore large variations in the time between subsequent assessments are to be expected. Also, each contributing clinical partner will have differences in how they perform routine clinical care for pwMS, thus the data available will also differ between the individual centers. The endpoints chosen for this study reflect the quality assessments that will be performed on these data, assessing its usefulness for the development of AI models and biomarkers related to disease progression.

Data representativeness will be assessed as one of the endpoints as we are working with clinical centers in Europe, which might result in an underrepresentation of certain demographic groups of patients. This could potentially lead to bias in the AI-driven models, resulting in suboptimal AI model predictions for these groups of patients. Secondly, in an observational setting, disease-modifying therapies are given to patients according to guideline recommendations and patient presentation. Observational data is therefore biased by these guidelines, and appropriate measures will be put in place to control for this bias when developing the AI models.

Typically, clinical trial data is of higher quality, in terms of data points available and the quality of the data set, which is tremendously beneficial when developing an AI model. For example, MRI scans that are acquired in clinical trials use a harmonized and up-to-date protocol and includes all necessary sequences. In addition, follow-up scans are obtained within a specific timeframe, on the same scanner, and with the same sequences. However, as ultimately the goal is to develop predictive models that can work in a clinical routine setting, it is important to also include real-world data during the development and validation of these AI models. Otherwise, when built based on a clinical trial data set only, these models will not be able to be incorporated into routine clinical care.

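### Representativeness for the MS population is worded for the whole pooled database and judges age by its range, so it can miss under-representation of older routine-care patients

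*Protocol article*

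**What the plan says.** The Endpoints section of the protocol article lists, among the criteria for a sufficiently high-quality database, "The representativeness of the harmonized dataset for the MS patient population as evaluated by age range, gender balance, the distribution of country of residence", and completes the list with "the distribution of race/ethnicity and the distribution of educational level". That makes five demographic items. Age is judged by range and gender by balance; the other three are judged by distribution. The sentence names no subset, no split by data source and no reference population.

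The content of the assessed dataset is fixed elsewhere:

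- Inclusion/exclusion criteria: "Participants must have a confirmed diagnosis of MS, NMOSD, MOGAD, CIS or RIS". Patients under 18 are excluded.
- Participants: "We expect the inclusion of the majority of records of ±7,000 patients from real-world routine clinical care and observational studies", and then "This will be supplemented with data from randomized controlled trials from ±4,000 patients".
- Study design: routine-care data, observational-study data and trial control-arm data go into one database.

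The Discussion gives the reason for the endpoint. Recruiting from European centres may leave some demographic groups under-represented, and models could then predict less well for them. It also expects the sources to differ: "Typically, clinical trial data is of higher quality, in terms of data points available and the quality of the data set". A separate endpoint is "The data completeness of each variable in the harmonized database", again worded for the pooled database.

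**The concern.** The set assessed and the target population do not match. The target is patients with MS, and the Discussion says that the models are meant for routine care. The dataset as worded adds two groups outside that target: NMOSD and MOGAD patients, whom the Participants section includes because they help to tell those diseases apart from MS, and trial patients, who were selected by trial eligibility rules.

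The age criterion has its own weakness. A range depends on the youngest and the oldest patient only, and the lower end is effectively fixed by the exclusion of under-18s. In a sample of about 11,000 adults it says little about how many patients are old or young. Age is a demographic characteristic, so this weakness falls within the purpose that the Discussion states. The check could look satisfactory while older routine-care patients are under-represented.

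**Working it through.** The plan gives no figure to reproduce here, and the Sample size section states that no calculation was possible. Three checks apply.

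**1. Share of trial patients.** Inputs from Participants: about 7,000 real-world and 4,000 trial patients. The article expects most, not all, of the real-world records, so let f be the fraction entering (the values of f below 1 are assumptions).

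Share = 4,000 / (4,000 + f × 7,000)

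| f | Total | Trial share |
|---|---|---|
| 1.00 | 11,000 | 36.4% |
| 0.75 | 9,250 | 43.2% |
| 0.50 | 7,500 | 53.3% |

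**2. Share of NMOSD/MOGAD.** The article gives no number. If they were 1% to 20% of the 7,000 (assumption), that is 70 to 1,400 patients, or 70/11,000 = 0.6% to 1,400/11,000 = 12.7% of the total.

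**3. Response of the age range.** One part needs no assumption: adding patients to a set can widen its range or leave it unchanged, but never narrow it. Pooling a younger group with the clinic patients therefore cannot show up as a loss at the upper end.

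For size, ages were simulated with n = 11,000, averaging 50 repetitions. Every age distribution is an assumption. Clinic ages are normal with SD 12, truncated to 18–85; trial ages are normal with mean 37 and SD 9, truncated to 18–55.

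Shifting the mean of a single population:

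| Nominal mean | Observed range | Share aged 55 or over |
|---|---|---|
| 38 | 18–82 | 8% |
| 43 | 18–84 | 16% |
| 48 | 18–85 | 28% |
| 53 | 18–85 | 43% |

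Mixing trial patients into a clinic population with nominal mean 48, total held at 11,000:

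| Trial share | Observed range | Mean age | Share aged 55 or over |
|---|---|---|---|
| 0% | 18–85 | 48.2 | 28.0% |
| 36.4% | 18–85 | 44.1 | 17.9% |
| 53.3% | 18–84 | 42.2 | 13.1% |

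The last column can be checked by hand. The assumed trial group adds no one above 55, so the pooled share is (1 − trial share) × 28.0%: 0.636 × 28.0% = 17.8% and 0.467 × 28.0% = 13.1%.

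The assumed cap of 85 limits how far the upper end can move, so the first table partly reflects that cap. The mixing result does not rest on it, because the oldest patients come from the clinic group in every row.

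**The case against.** The other side has real force.

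- **Condensed article.** The text does not say that NMOSD and MOGAD patients will be counted in this comparison, or that only pooled results will be shown. Strata and a reference registry may be in the full protocol. This stands as a caution. But the article does fix the dataset, the target and the age measure, and where it means centre level or control arms, the same section says so.
- **The other four items.** Age range is one criterion of five, and three of the others are full distributions. This stands: the weakness in the measure concerns age only.
- **CIS and RIS.** The Participants section includes them as very early MS. Only NMOSD and MOGAD are clearly outside the target.
- **Disease characteristics.** The stated purpose is demographic, and the Study report section promises a description that covers MS history, MRI and treatment history. Leaving them out of the endpoint therefore does not defeat it; adding them is an extension.

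A reader might infer three stronger points that the article does not support. The first is that the endpoint cannot show whether the models will transfer to practice. The plan does not claim that it does; model validation is a separate activity under Biomarker and AI model development. The second is that country of residence is a faulty criterion because the centres fix it. The Discussion openly acknowledges the European restriction, and documenting it is not an error. The third is that pooled completeness must overstate real-world completeness by a known amount. No completeness figures are given, and for a variable that the trials did not collect, pooling would understate it.

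**Conclusion.** The point holds in a limited form. Followed as written, the endpoint compares a mixed dataset with the MS population, and trial patients are about 36% of that dataset or more. Its age criterion cannot reveal dilution of the clinic population by a younger group. That is enough for it to miss under-representation of older patients, inside its own demographic purpose. The trial share follows from the article's counts. The drop from 28% to 18% aged 55 or over is illustrative and depends on trial patients being younger than clinic patients, which the article does not state. The NMOSD/MOGAD contribution cannot be sized from the article. This is a specific and cheap improvement to an endpoint; it does not invalidate the database.

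**What to change.** Reword the endpoint so that representativeness is assessed in real-world patients with MS, with CIS and RIS shown as early disease, and with trial patients and NMOSD/MOGAD patients in separate columns. Replace age range with the age distribution. Add MS phenotype, disease duration, EDSS and class of disease-modifying treatment as further descriptors, drawn from the disease and treatment data that the study already collects. Report the completeness of each variable by source (real-world and trial) as well as pooled, because the Discussion expects the sources to differ.

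The cost is a change of wording and some stratified tables, with no new data collection. Some headline figures may look less favourable.

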### Outcome parameters

While there is no minimum nor a limit of the observational time required for patients, on average, retrospective data spanning up to 10 years is anticipated, provided the data quality is sufficiently high. When choosing data and variables of interest for the study, relevance for the development and optimisation of the AI-based models was balanced with feasibility of acquiring this data during routine clinical care. The categories of data we collect consist of:

Patient-specific data: demographics, comorbidities and risk factorsDisease-specific data: disease history, disease status, relapse history and visual testsSubclinical data: magnetic resonance imaging (MRI) from brain and spinal cord, Optical coherence tomography (OCT) and Evoked potentials (EP)Treatment history: disease-modifying treatments (DMT) and non-pharmaceutical treatments (NPT)

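### Temporal uniformity is assessed by the average interval between assessments, which measures how often patients are assessed, not how evenly

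*Protocol article*

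**What the plan says.** The Endpoints section of the protocol article uses temporal uniformity in four places. Three of them rest on an average interval:

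- Harmonized dataset (quality criteria): "The temporal uniformity of the harmonized dataset over time as assessed by the average time between subsequent assessments of each variable".
- MRI (feasibility criteria): uniformity is judged by "the comparability of MRI scans and the average time between subsequent MRI assessments for each patient".
- EDSS, functional systems score, T25FWT, 9HPT and SDMT (feasibility criteria): each score is examined for erroneous entries, "as well as for the average time between subsequent assessments of each variable".

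The fourth, for each institution's data, is judged "as assessed by the number of changes to variables over time". That concerns changes in what is recorded and how, not when patients are assessed. A further endpoint is "The data completeness of each variable in the harmonized database", which does not measure spacing either.

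The Discussion says that in routine care "large variations in the time between subsequent assessments are to be expected", and presents the endpoints as the quality assessments made on such data. The Outcome parameters section sets no minimum observation time and states that "on average, retrospective data spanning up to 10 years is anticipated".

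**The concern.** Uniformity over time is a statement about spread: whether assessments come at similar intervals or in clusters separated by gaps. A mean interval is a statement about frequency. The article names the first property and fixes a measure of the second. It also identifies variable intervals as a known difficulty of these data, then chooses a statistic that averages the variation away.

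At stake is whether the endpoints can do their job. They are meant to show whether the database can support longitudinal progression models and imaging biomarkers. A variable assessed evenly through follow-up and one assessed in two bursts years apart can produce the same reported figure, and a reader of the study report could not tell them apart.

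**Working it through.** The article gives no figure for this endpoint, so there is nothing to reproduce. The check is algebraic, with illustrations. The number of assessments and their spacing below are assumptions. The 120-month span is the upper end of the anticipated 10 years.

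**Identity.** For assessment times t1 < … < tn, the intervals sum to tn − t1, so

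mean interval = (tn − t1)/(n − 1).

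Only the first date, the last date and the count enter. This carries over to a group of patients. Averaging patient means gives the mean of span/(n − 1). Averaging all intervals gives total span divided by total number of intervals. Neither depends on where the intermediate assessments fall, so the point does not turn on how patients are weighted.

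**Illustration over 60 months, ten intervals.**

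- Regular: 10 × 6 = 60; mean 6.0; SD 0.
- Clustered: 9 × 1 + 51 = 60; mean 6.0; SD = √[(9 × 5² + 45²)/9] = √(2250/9) = √250 = 15.8.

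**Illustration over 120 months, 21 assessments (20 intervals).** All times are in months.

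| Spacing | Mean | SD | CV | Longest gap |
|---|---|---|---|---|
| Regular, 6-monthly | 6.0 | 0 | 0 | 6 |
| Drift: 15 intervals of 4, then 5 of 12 | 6.0 | 3.6 | 0.59 | 12 |
| Two 3-monthly runs, one gap (19 × 3 + 63) | 6.0 | 13.4 | 2.24 | 63 |
| Two monthly runs, one gap (19 × 1 + 101) | 6.0 | 22.4 | 3.73 | 101 |

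The mean is constant while the CV runs from 0 to 3.73 and the longest gap from 6 to 101 months.

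**The reverse failure.** Regular 6-monthly and regular 12-monthly series both have SD 0, yet average 6.0 and 12.0 months. The metric differs where uniformity does not.

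**Missed visits.** If a 6-monthly patient misses ten consecutive visits within 120 months, 11 assessments remain: nine intervals of 6 and one of 66. The mean rises to 120/10 = 12.0 months. The gap does move the figure, but the result is the same as for a regular 12-monthly schedule.

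**The case against.** The best defence has four parts.

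**The average is not empty.** A reader might infer that it carries no information on uniformity at all. That is too strong. The exact tie holds for equal span and count, and averages compared across periods, centres or patients can reveal some unevenness: the drifting series above averages 4.0 months in its first 60 months and 12.0 in its second. The MRI endpoint is already an average "the average time between subsequent MRI assessments for each patient", which yields a distribution across patients, and it is paired with scan comparability. This stands as a limit on the wording. It does not rescue the metric, because the article specifies no comparison by period or centre, and a per-patient mean still hides spacing within that patient.

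**A condensed article may leave detail to the full protocol.** This holds for weighting. If half the patients are seen every 3 months and half every 12 months for 5 years, the mean over all intervals is (20 × 3 + 5 × 12)/25 = 4.8 months and the mean over patients is (3 + 12)/2 = 7.5. A reader might infer that frequently seen patients dominate the result. However, the article does not say that intervals are pooled, and for MRI it says otherwise. The defence fails for the main point, because the article does name the metric, and the named metric does not measure the named property.

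**The consequences can be overdrawn.** A reader might infer that the database could be wrongly declared uniform, or that RAW and PIRA classification would fail for lack of closely spaced confirmatory assessments. The article states no threshold for uniformity and no confirmation rule or interval for RAW or PIRA. It also does not say that frequently seen patients are those with relapses. None of these inferences is supported.

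**Nothing is irreversible.** There is no hypothesis test, and the dates needed for the average are the same dates needed for a measure of spread. This stands, and it bears on severity.

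**Conclusion.** The point holds in limited form. In all three endpoints that use it, the average interval measures assessment frequency and cannot show within-patient spacing. That follows from the identity and needs no assumption. The sizes shown (for example SDs of 0 and 15.8 months behind the same 6.0-month mean) rest on assumed schedules and say what could be hidden, not what these data will contain. For MRI the defect is narrower, since the average is per patient and comparability is assessed as well. The harm is an uninformative endpoint rather than a demonstrated wrong conclusion, so this is a correction of low to moderate severity.

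**What to change.** In the Endpoints section, for every repeatedly assessed variable covered by the three endpoints, including OCT and evoked potentials as well as MRI and the disability scores:

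1. Keep the average interval, and label it a measure of assessment frequency.
2. Add a within-patient measure of spread of the intervals (SD, IQR or coefficient of variation) and the longest gap, each summarised across patients. The longest gap should not be dropped if the IQR is chosen: with nine 1-month intervals and one of 51 months both quartiles are 1, so the IQR is 0, as for a perfectly regular series.
3. Report these separately for routine-care and trial data. The Discussion says trial follow-up scans are made to a set timeframe while routine-care timing varies, so one combined figure would describe neither.
4. State the number of patients with fewer than two assessments of the variable, who contribute no interval. Those with exactly two have one interval and no within-patient spread, and are worth counting too.

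The cost is a change of wording and a few extra summary columns from dates already collected. No new data are needed.
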